#### 4.2.2 Sample size

The proposed study is a randomized controlled exploratory trial aimed at providing preliminary insights into the comparative outcomes of two independent groups. As formal power calculations are not mandatory for exploratory studies, a two-sample t-test formula for comparing means was applied primarily to provide a rational basis for determining a feasible sample size:

$$n=\frac{2\,s_{p}^{2}\,{\left[Z_{1-\alpha /2}+Z_{1-\beta }\right]}^{2}}{\mu_{d}^{2}}$$

This formula incorporates the pooled variance, the anticipated mean difference between groups, the significance level (α), and statistical power (1−β). Using estimates from published data, the pooled variance (sp^2^) was taken as 2.85, and the expected mean difference (μd) between groups as 1.83. For reference, a two-sided test with a significance level of 0.05 (Z = 1.96) and a nominal power of 90% (Z = 1.28) was considered. Substituting these values yielded a preliminary estimate of approximately 18 participants per group. Allowing for an anticipated dropout rate of 20%, the adjusted number was approximately 23 participants per group, resulting in a total sample size of 46.

#### 4.2.3 Recruitment

To facilitate the recruitment of participants for the study, a comprehensive and multi-faceted awareness campaign will be implemented. This initiative will include two primary components: educational programs and the distribution of informational posters. We will also utilize digital advertisements on various platforms. The purpose of these programs is not only to inform the public about the study but also to raise general awareness about Premenstrual Syndrome (PMS), thereby assisting in the identification of individuals who may be experiencing symptoms. These preliminary initiatives, along with our recruitment channels, have all been approved by the Institutional Ethics Committee. This will be followed by a preliminary screening process, which will be conducted using a Google Form to accurately ascertain the presence of PMS symptoms among potential participants. Furthermore, to uphold ethical standards and avoid any potential for perceived coercion or undue influence, we will not target students only from our university. Individuals identified with such symptoms will be encouraged to seek consultation at the Outpatient Department (OPD) of the Amrita School of Ayurveda, located in Clappana, Kollam, Kerala. Subsequent recruitment into the study will be contingent upon the fulfillment of established inclusion criteria and the completion of the consultation process at the designated study center.

### 4.3 Randomization and allocation sequence generation

Participants who meet the inclusion criteria and complete the initial consultation at the Outpatient Department (OPD) of Amrita School of Ayurveda, Clappana, Kollam, Kerala, will be considered for enrolment. To ensure balanced group sizes and minimize selection bias, participants will be randomly allocated to either the Trial group (CBT + *Brahmi*) or the Control group (CBT + Placebo) using fixed block randomization with a block size of 4. A total of 11 blocks will be formed to accommodate the planned sample of 44, and the remaining two participants will be randomly assigned to any of the existing blocks. The randomization sequence will be generated by the Medical Officer at the Amrita School of Ayurveda. This individual is not involved in participant recruitment, intervention delivery, or outcome assessment, which ensures balanced group sizes throughout enrolment and maintains the internal validity of the study.

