## Abstract

Premenstrual syndrome (PMS) is a widespread and under-recognized disorder, characterized by cyclical recurrence of physical, psychological, and behavioral symptoms during the luteal phase, significantly impacting the daily functioning of women. Cognitive Behavioral Therapy (CBT) is an established non-pharmacological strategy for PMS, while *Brahmi* (Bacopa monnieri), a classical Ayurvedic herb, has traditionally been used to enhance cognition, reduce anxiety, and support emotional balance. This exploratory study evaluates whether combining *Brahmi* with CBT offers additional benefit compared to CBT alone. It is a double-blind, randomized, placebo-controlled exploratory clinical trial (CTRI/2025/02/081239) conducted at the Amrita School of Ayurveda, Kollam, Kerala, with sponsorship from the Central Council for Research in Ayurveda Sciences (CCRAS). Forty-six women aged 18–24 years, diagnosed with moderate to severe PMS using the Premenstrual Symptoms Screening Tool (PSST) and the Daily Record of Severity of Problems (DRSP), will be recruited and randomly assigned to receive either CBT with *Brahmi* tablets or CBT with placebo tablets. The primary outcomes include reduction in PMS severity, assessed by DRSP, and improvement in quality of life measured with the Quality of Life Enjoyment and Satisfaction Questionnaire (Q-LES-Q SF). Secondary outcome is reduction in functional disability measured using the Sheehan Disability Scale. Assessments will be conducted at baseline, during treatment, and at follow-up. Statistical analysis will be carried out using repeated measures ANOVA with Bonferroni-adjusted post hoc tests, significance set at *p* < 0.05, and effect sizes reported. A limitation of this design is that it cannot disentangle the individual effects of *Brahmi* from CBT, allowing conclusions only on the combined intervention. The study aims to generate preliminary exploratory evidence for a safe, integrative, and accessible approach to PMS management in young women.

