## 3 Methods

### 3.1 Trial design

This study is a double-blind, placebo-controlled, randomized exploratory clinical trial designed to generate preliminary observations on feasibility, safety, and potential signals of *Brahmi* (Bacopa monnieri) tablets as an adjunct to Cognitive Behavioral Therapy (CBT) in managing Premenstrual Syndrome (PMS). Eligible participants will be randomly assigned to one of two groups: the trial group (CBT plus Brahmi) or the control group (CBT plus placebo). Randomization will be performed using a fixed block design with a block size of four to ensure balanced group sizes, with the sequence generated by a computer algorithm and maintained by a Medical Officer who is not involved in participant recruitment, intervention delivery, or outcome assessment. Both participants and study personnel involved in delivering CBT, assessing outcomes, and analyzing data will remain blinded to group assignments, ensuring methodological rigor and minimizing potential bias throughout the exploratory trial.

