### 4.4 Allocation concealment mechanism

A block randomization sequence will be generated by the statistician to ensure balanced allocation between the Brahmi and placebo arms throughout the trial. Based on this sequence, the Medical Officer (who is not involved in assessments) will prepare sequentially numbered, identical, opaque, sealed medication packages. Each package will be coded according to the randomization list but will appear identical in external characteristics, thereby concealing its contents.

At enrolment, participants will receive the next available sequentially numbered package, ensuring strict adherence to the block randomization order. The Principal Investigator, Co-investigators, CBT practitioners, Statistician, and participants will remain blinded to the allocation. The intervention codes will only be revealed after the completion of all post-intervention assessments or earlier in the event of a medical emergency that requires unblinding.

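### Section 4.3 lists 44 allocations for a planned 46 and places the last two in blocks that are already full, which gives them no arm

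*Protocol article*

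**What the plan says.** The planned total is 46. The Abstract gives it as "Forty-six women aged 18–24 years", and section 4.2.2 (Sample size) derives it: "the adjusted number was approximately 23 participants per group, resulting in a total sample size of 46".

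The block size is four and does not vary. Section 3.1 (Trial design) says "Randomization will be performed using a fixed block design with a block size of four to ensure balanced group sizes", and section 4.3 (Randomization and allocation sequence generation) repeats it: "using fixed block randomization with a block size of 4".

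Section 4.3 then sets the number of blocks, "A total of 11 blocks will be formed to accommodate the planned sample of 44", and deals with the remainder in the same sentence: "the remaining two participants will be randomly assigned to any of the existing blocks".

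Section 4.4 (Allocation concealment mechanism) describes sealed, numbered packages prepared from the list. At enrolment "participants will receive the next available sequentially numbered package, ensuring strict adherence to the block randomization order". Section 4.5 (Implementation and blinding) likewise has the Medical Officer assign participants from a block sequence drawn up in advance.

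**The concern.** A permuted block of four at 1:1 holds two allocations to each arm. Once it is filled, it has no open place. To say that a 45th participant joins an existing block therefore does not say whether she receives Brahmi or placebo. It also turns that block into a block of five or six, against the fixed size in sections 3.1 and 4.3.

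The rule also clashes with sections 4.4 and 4.5. A list of 11 blocks produces 44 numbered packages, so there is no next package for participants 45 and 46.

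Two things are at stake. The allocation procedure cannot be reproduced from the text for those two participants. And if they are allocated outside the pre-packed sequence, the concealment described in section 4.4 does not cover them. Section 4.3 gives balance and low selection bias as the reasons for blocking, and for these two allocations the rule secures neither.

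**Working it through.** **Inputs.** From section 4.2.2: pooled variance 2.85, mean difference 1.83, Z values 1.96 and 1.28, dropout 20%. From sections 3.1 and 4.3: block size 4. From section 4.3: 11 blocks.

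**1. The plan's total reproduces.**

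- n per group = 2 × 2.85 × (1.96 + 1.28)² / 1.83² = 17.87, rounded up to 18.
- With dropout: 18 / (1 − 0.20) = 22.5, rounded up to 23 per group.
- Total = 2 × 23 = 46, as stated.

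**2. Places on the list.**

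- 46 = 11 × 4 + 2, so 11 blocks hold 44 and the shortfall is 2.
- 2 / 46 = 4.3% of allocations.
- After 44 enrolments every block stands at 2:2 and the trial at 22:22. No place is open in any block.

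**3. Resulting split.** The text gives no probability for the last two arms, so a mechanism has to be assumed. With two independent 1:1 tosses:

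- one to each arm (23:23): probability 2 × 0.5 × 0.5 = 0.50;
- both to the same arm (24:22 or 22:24): probability 0.5² + 0.5² = 0.50.

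**4. Effect on power.** Normal approximation at the plan's inputs, all 46 analysed: power = Φ(1.83 / √[2.85 × (1/n₁ + 1/n₂)] − 1.96).

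- 23:23 gives 95.69%.
- 24:22 gives 95.66%.

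The difference is 0.03 percentage points.

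**5. Lists that would cover 46.**

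| List | Positions | Chance of 23:23 |
|---|---|---|
| 11 blocks of 4 + 1 block of 2 | 44 + 2 = 46 | 1 |
| 7 blocks of 4 + 3 blocks of 6 | 28 + 18 = 46 | 1 |
| 12 blocks of 4, first 46 used | 48, two unused | 4/6 = 0.67 |

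In the last row, a block of four has 6 possible orders, and in 4 of them the first two places go to different arms.

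**The case against.** The best defence has four parts.

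**The total is accounted for.** The sentence that mentions 44 goes on to mention two more, so section 4.3 does add up to 46. This stands. Calling 44 the planned sample is loose wording, and 11 × 4 = 44 is correct. The defect is the rule for a known remainder. Changing 44 to 46 without changing the blocks would create a new error, because 11 blocks of four do not hold 46.

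**The two extra places might be built into the list when it is generated.** The sentence sits in the section on sequence generation and can be read as enlarging one or two blocks in advance. All 46 packages could then be numbered beforehand, and sections 4.4 and 4.5 would hold. This reading is possible, so the conflict with those sections is certain only for an 11-block list of 44. Even on this reading, the fixed size of four is broken and the arms of the added places remain undefined.

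**Allocation by someone who knows the list is not stated.** A reader might infer that the Medical Officer, who holds the codes, would choose the last two arms ad hoc. The document does not support that as fact. Section 4.3 says the assignment is random and does not say when or by whom it is made. Under section 4.5 a blinded principal investigator alone enrols, and section 4.3 keeps the Medical Officer out of recruitment and outcome assessment. So even on the worst reading, nobody who knows the list chooses who enters the trial.

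**The numerical effect is trivial.** This stands. Section 4.2.2 gives 23 per group only as approximate and allows 20% dropout, and section 4.7 presents P values descriptively.

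It might also be argued that an article may leave such detail to the full protocol. That would excuse silence, but here the article states a rule, and the rule does not work.

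**Conclusion.** The rule for participants 45 and 46 is wrong as written. It gives them no arm and breaks the fixed block size of 4. If the list consists of 11 blocks, it also leaves them no numbered package, contrary to sections 4.4 and 4.5.

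The point is minor. It touches two of 46 allocations. The 0.50 probability of a 24:22 split rests on an assumed pair of independent coin tosses, and a split of that size is the most uneven that two extra participants can produce from 22:22. Its effect on power is negligible. The loss of concealment is conditional: it arises only if the two are allocated outside the list, which the text neither states nor rules out. The document supports neither a claim that allocation will be compromised nor a claim that the trial will be materially unbalanced.

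**What to change.** In section 4.3, describe the planned sample as 46, delete the sentence that sends the last two participants to existing blocks, and state that all 46 positions are generated and packaged before first enrolment. Then name one of these lists:

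- **11 blocks of four plus one block of two**, the short block at a position concealed from recruiting staff. This gives exactly 23:23 and is the smallest change.
- **Randomly ordered blocks of 4 and 6 totalling 46**, for example 7 × 4 + 3 × 6. This also gives exactly 23:23, but replaces the fixed block size.
- **Twelve blocks of four, using the first 46 packages.** This keeps the fixed size and the concealed sequence, but gives 23:23 only with probability 4/6.

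Sections 3.1 and 4.3 should describe the block sizes in the same way after the change.

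The cost is almost nothing if the list has not been made. If it already exists, append one block, generated and packaged in advance like the rest. A block of two secures 23:23, provided the first 11 blocks are filled; a block of four cut after two does not.

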### 4.4 Allocation concealment mechanism

A block randomization sequence will be generated by the statistician to ensure balanced allocation between the Brahmi and placebo arms throughout the trial. Based on this sequence, the Medical Officer (who is not involved in assessments) will prepare sequentially numbered, identical, opaque, sealed medication packages. Each package will be coded according to the randomization list but will appear identical in external characteristics, thereby concealing its contents.

At enrolment, participants will receive the next available sequentially numbered package, ensuring strict adherence to the block randomization order. The Principal Investigator, Co-investigators, CBT practitioners, Statistician, and participants will remain blinded to the allocation. The intervention codes will only be revealed after the completion of all post-intervention assessments or earlier in the event of a medical emergency that requires unblinding.

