### 4.5 Implementation and blinding

Participant recruitment and enrolment will be conducted solely by the PI at the designated OPD. The Medical Officer will implement the randomization by assigning participants to the trial or control group according to the pre-generated block randomization sequence and dispensing the corresponding medication packages. Cognitive Behavioral Therapy (CBT) sessions will be delivered by certified CBT therapists who remain blinded to participant group assignments. A Co-Investigator will be responsible for assessing the outcomes, and they will also remain blinded to the group assignments. The Statistician will be responsible for data analysis and will also remain blinded until the study is complete.

This study employs a double-blind exploratory design to minimize bias. The following personnel will remain blinded throughout the trial:

**Participants:** will be unaware of whether they are receiving *Brahmi* or placebo tablets.**Principal Investigator (PI):** blinded to group allocation to prevent selection and performance biases.**CBT therapists:** administer therapy sessions without knowledge of group assignments to ensure uniformity of intervention delivery.**Co-Investigator:** conducts the outcome assessments while blinded to group allocation.**Statistician:** conducts data analysis blinded to allocation until study completion to reduce analytical bias.**Medical officer:** handles randomization and medication assignment, maintains the confidential coding system, and decodes interventions only after final data analysis or in case of emergency unblinding.

This structured approach ensures rigorous randomization, allocation concealment, and blinding, thereby maintaining methodological integrity and minimizing potential biases throughout the trial.

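### Sections 4.3 and 4.4 name different generators of the randomisation list, and if 4.4 is followed with an unmasked list the stated blinding of the analysing statistician does not hold

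*Protocol article*

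**What the plan says.** **Who generates the list.** Section 4.3: "The randomization sequence will be generated by the Medical Officer at the Amrita School of Ayurveda". Section 4.4, directly after it: "A block randomization sequence will be generated by the statistician to ensure balanced allocation". In 4.4 the Medical Officer only prepares the packages from that list. Section 3.1 describes the process as "with the sequence generated by a computer algorithm and maintained by a Medical Officer".

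**Who analyses, and whether blinded.** Section 4.4 counts the statistician among those kept blind. Section 4.5 says that the statistician "conducts data analysis blinded to allocation until study completion to reduce analytical bias". Section 4.6.7 again calls the statistician blinded and assigns all analyses to that role. Section 4.9 gives the analyses to an independent biostatistician, without saying whether this is the same person.

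**What the Medical Officer does.** Section 3.1 describes this person as someone "who is not involved in participant recruitment, intervention delivery, or outcome assessment", and 4.3 repeats the point. Section 4.5 has the same person "assigning participants to the trial or control group according to the pre-generated block randomization sequence and dispensing the corresponding medication packages". The Medical Officer also appears in 4.5's list of staff who stay blinded for the whole trial, in an entry that makes this person keeper of the code.

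**When the code is released.** Section 4.4: "The intervention codes will only be revealed after the completion of all post-intervention assessments", or earlier in a medical emergency. Section 4.5 says that the Medical Officer "decodes interventions only after final data analysis or in case of emergency unblinding".

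**The concern.** Two consecutive sections give one task to two people, so both cannot be followed. The choice between them matters. Under 4.3 the list is made by someone who must know the code anyway. Under 4.4 it is made by the role that is promised to be blinded and that analyses the data.

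Analyst blinding has real work to do in this trial. Section 4.7 says that repeated measures ANOVA or mixed-effects models may be applied. Section 4.8 permits optional subgroup and adjusted analyses. Section 4.9 presents intention-to-treat and per-protocol results, with complete cases as the primary approach to missing data and mixed models as a further option. An analyst who knows the allocation could choose among these after seeing which favours an arm. With 46 participants planned and effect sizes as the main output, such choices can move the reported estimates.

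**Working it through.** The point involves no calculation, so the check sets the role statements side by side.

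| Question | Section 3.1 | Section 4.3 | Section 4.4 | Section 4.5 | Section 4.6.7 |
|---|---|---|---|---|---|
| Who generates the list? | A computer algorithm; Medical Officer maintains it | Medical Officer | Statistician | Not stated; list already exists | – |
| Is the statistician blinded? | Staff analysing data are | – | Yes | Yes | Yes |
| Does the statistician analyse? | – | – | – | Yes | Yes, all analyses |
| Is the Medical Officer part of intervention delivery? | No | No | Prepares packages | Assigns and dispenses | – |
| Is the Medical Officer blinded? | – | – | Not among those named | Listed as blinded, yet keeps the code | – |
| When is the code released? | – | – | After the last assessment | After final analysis | – |

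1. **Generator.** Sections 4.3 and 4.4 conflict. Section 3.1 does not settle it, because someone has to run the algorithm and keeping a list is not the same as making it.

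2. **Consequence under 4.4.** A person who generates a list with treatment names knows the allocation of everyone on it. Supplying that person with A/B-coded data later would not restore blinding, because the coded groups can be matched to the list. Two arrangements would preserve blinding: a list that carries only masked codes with the key held elsewhere, or a second statistician for the analysis. The document states neither.

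3. **Consequence under 4.3.** The conflict over the analyst disappears, because the Medical Officer is already unblinded by keeping the code.

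4. **Medical Officer's status.** Someone who keeps the code and assigns by the sequence cannot be on a list of blinded staff. Dispensing the study tablets is also hard to square with having no part in intervention delivery.

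5. **Code release.** The condition in 4.4 is met once the last assessment is done, which is before analysis. The condition in 4.5 is met only after it. Applied alone, 4.4 would let the analyst's blinding lapse before analysis begins, whoever made the list.

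6. **Other roles.** Section 3.4 describes tablets and packaging identical in appearance. Section 4.4 describes identical, opaque, sealed and numbered packages. Section 4.5 leaves enrolment solely to the blinded Principal Investigator and assessment to a blinded Co-Investigator. None of this depends on who generates the list.

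**The case against.** The best defence is that the statistician of 4.4 may have produced a list of bare codes, with the Medical Officer holding the key, or that the independent biostatistician of 4.9 is a second person. Either would keep the analyst blind. Section 4.5 does give the Medical Officer a confidential coding system, which fits the first reading. These readings are possible but not stated, so the failure of analyst blinding is conditional on an unmasked list in the analyst's hands. Nor can one say that all 46 allocations would be on that list: 4.3 builds 11 blocks of 4, which is 44, and handles the remaining two participants separately.

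On code release, the two rules are not strictly incompatible. Section 4.4 sets an earliest point, and release after final analysis satisfies both sections. What remains is that 4.4 by itself permits release before analysis.

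On weight, 4.7 makes the analysis descriptive without inferential claims, and section 6 disclaims proof of effectiveness. The Abstract also names repeated measures ANOVA, which narrows the model choice, although 4.7 reopens it. This lowers the stakes but does not remove the contradiction, since the effect estimates are meant to guide later trials.

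A reader might go further and infer that the trial is not double-blind, or that an unblinded dispenser could influence every participant-completed outcome. The document does not support either. Someone has to hold the code, and handing out sealed, identical packs is not in itself a flaw. Section 4.5.1 also forbids written or verbal disclosure of the code. The fault over the Medical Officer lies in how the role is described.

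**Conclusion.** The point holds in a limited form and is wrong as written.

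- The contradiction over who generates the list is certain from the text.
- The loss of analyst blinding follows if 4.4 is the version carried out, the list shows treatment, and the same statistician analyses. The document rules out none of these.
- The Medical Officer's place on the blinded list is wrong on its face, and the description in 3.1 and 4.3 conflicts with 4.5.
- The code-release point is not fixed to one moment, and one of the two statements allows unblinding before analysis.

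The size of any bias cannot be derived from the document. The exposure is to analyst choice across the three outcome scales, not to how participants, therapists or the assessor behave. It should be settled before the list is generated, because knowledge of the allocation cannot be taken back.

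**What to change.** 1. Name one generator who is not the analyst, and use the same wording in 3.1, 4.3, 4.4 and 4.5. The Medical Officer is a natural choice, being already unblinded.
2. First establish whether a list already exists. Ethics approval dates from January 2025 and the tablets are described as procured, so it may. If the statistician has generated it, do not simply delete the sentence: report this and have the primary analysis done by someone without access to the list.
3. State that the analyst receives only A/B group codes.
4. Take the Medical Officer off the blinded list in 4.5, and correct the statement in 3.1 and 4.3 so that it agrees with the dispensing role. Moving pack issue to another member of staff is not required.
5. Set one code-release point in 4.4 and 4.5: after database lock and completion of the A/B-coded analysis, with emergency unblinding as the only exception.

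The cost is protocol wording with existing staff, plus archiving of the randomisation program by the Medical Officer. If the statistician has already made the list, a second analyst is also needed.
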